### Power

The power calculation was based on a superiority calculation. Based on comparisons between the current and previous studies, considering differences between populations and interventions, and including experiences from clinical practice, an injury incidence of 20 % is expected in runners focusing on volume and an injury incidence of 35 % is expected in runners focusing on intensity [18, 19]. To be able to show a minimum difference in injury risk between groups of 5 %, a sample size of 620 participants is required to reach a power of 80 %. An accommodation to a potential loss to follow-up is necessary to include in determining the number of participants needed. In prospective studies with a self-structured running regime and a follow-up ≥ 6 months, the loss to follow-up have been reported to be approximately 22–30 % [34, 35]. Prospective studies with a structured running regime, and follow-up periods of 13 weeks, reported the loss to follow-up to be approximately 8 and a 60 % completion of the scheduled running [12, 19]. Taking into consideration the duration of the 24-week follow-up period in the present study, and the motivational factor possibly associated with a structured running regime, a potential loss to follow-up of 15 % is hypothesized, which leads to a required sample size of 713 participants.

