### Statistical analysis

All data will be analyzed using an instrumental variable approach in the primary analysis [36]. The instrumental variable is the randomization. Secondary analyzes are intention-to-treat and per-protocol. Time to first injury is analyzed using the following primary time scale: calender time in days and weeks. Data will be analyzed at the following time-points: 2 weeks, 4 weeks, 8 weeks and 16 weeks after randomization. Secondary time scales are cumulative running volume in kilometres and cumulative running volume in minutes. Time of follow-up begins when the randomized interventions start. The unit of analysis is each participant. Participants will be right-censored in case of pregnancy, disease, lack of motivation, non-running-related injury causing a permanent stop of running, unwillingness to attend clinical examination in case of injury, if more than 10 % of all training sessions were uploaded manually (they will be censored at the time 10 % of uploads are manual) or at end of follow-up, whichever comes first.

The injury proportion as a function of the follow-up time scales mentioned above will be estimated using the Kaplan-Meier curve. The cumulative injury risk difference between groups is analyzed, performing a generalized linear regression, using the pseudo values method [37]. Competing risk analysis will be performed separately for both groups, to investigate difference in risk of hypothesized injuries including more than one endpoint [38]. The Aalen Johansen estimator will be applied in the competing risks analysis. Endpoints included in the competing risk analysis are non-running-related injury causing a permanent stop of running and the 20 injuries presented by Taunton et al. [13] In the intensity group (Sch-I) the risk of achilles tendinopathy, gastrocnemius injuries, and plantar fasciitis are analyzed in a competing risk model, treating the remaining 17 injuries as competing events. In the volume group (Sch-V) the risk of patellofemoral pain syndrome, iliotibial band syndrome, and patellar tendinopathy are analyzed in a competing risk model, treating the remaining 17 injuries as competing events [21]. Differences are considered statistically significant at *p* < .05, and estimates are presented with 95 % confidence intervals. All analyzes are performed using STATA/SE version 13 (or more if applicable).

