The superiority power calculation based on a minimum risk difference between groups of 5 %, and taking a hypothesized loss to follow-up of 15 % into account, revealed a required sample size of 713 participants to reach a power of 80 %. A predetermined inclusion period of 6 months has been determined. The challenge of including 713 participants over a 6 month period is acknowledged. However, the estimated 31 % of the adult population in Denmark who participates in recreational running, provides an approximate background population of 904.685 persons, from which recruitment of participants can take place (Based on numbers from Statistics Denmark) [45]. Information regarding the possibility of participation in the trial is announced through the two largest Danish recreational running organizations. Possible participants can easily access and fill out the inclusion/exclusion questionnaire and indicate their interest in participation. The baseline information is collected through the online training diary, making data collection less time consuming for both participants and investigators. This gives us reason to assume that such a large scale inclusion is possible. However, a sample size of 357 participants, based on a minimum risk difference between groups of 1 %, with a power of 80 % and taking the hypothesized loss to follow-up of 15 % into account, is the minimal acceptable number of included participants and also the minimal acceptable clinical relevant difference. At the end of the 6 month inclusion period, no additional inclusions will be made.

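### The recruitment target of 713 adds 15 % to 620 instead of dividing by 0.85, so it leaves 606 runners, not 620; the floor of 357 appears to carry the same slip, with a small effect on power

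*Protocol article*

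**What the plan says.** The Power section assumes that "an injury incidence of 20 % is expected in runners focusing on volume" and that "an injury incidence of 35 % is expected in runners focusing on intensity". With 5 % as the smallest difference that the trial should be able to detect, it states that "a sample size of 620 participants is required to reach a power of 80" (per cent). It then reviews loss rates in earlier running studies, settles on 15 % with the 24-week duration in mind, and concludes: "which leads to a required sample size of 713 participants".

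The Discussion repeats that the calculation "revealed a required sample size of 713 participants". It adds a floor of 357 included participants, tied to a 1 % minimum risk difference with the same power and the same 15 % loss, and allows no inclusions after the six-month recruitment period. Both targets are described there as numbers of included participants.

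Methods/design divides the 24-week follow-up into 8 weeks of preconditioning and 16 weeks of intervention. Under Statistical analysis the outcome is time to first injury, and "Time of follow-up begins when the randomized interventions start".

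**The concern.** If a fraction *d* of those recruited is lost, the number remaining is N × (1 − *d*). To keep 620 at *d* = 0.15, N must be 620/0.85. Multiplying by 1.15 always gives too few, so the stated required sample size does not meet its own requirement under its own loss assumption. The figure appears in two sections, and the floor, which the authors call the smallest acceptable number, seems to rest on the same step.

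A second matter bears on what the 15 % must cover. The targets count inclusions, but the analysed time starts 8 weeks later. A runner injured during preconditioning may not be available for a first injury after that point. The Power section does not say whether such runners are part of the 15 %.

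**Working it through.** **Inputs.** 620 required, 80 % power, incidences 20 % and 35 %, minimum difference 5 %, loss 15 % (Power); floor of 357 at 1 % (Discussion); equal groups (Randomization); p < .05 (Statistical analysis). Sidedness is not stated; two-sided is assumed.

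**1. The plan's 713.** 620 × 1.15 = 713.0, an exact match.

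**2. What 713 leaves.**
- 713 × 0.85 = 606.05, so 606, which is 14 short of 620.
- Largest loss that 713 can absorb: 1 − 620/713 = 13.0 %.
- Correct inflation: 620/0.85 = 729.4, so 730. Check: 730 × 0.85 = 620.5.

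**3. The basis of 620.** The 5 % works only as a superiority margin, with an effective difference of 0.35 − 0.20 − 0.05 = 0.10. At two-sided 0.05 and 80 % power, the size per arm is:
- unpooled variance: 304.1 (610 in total);
- pooled variance under the null, unpooled under the alternative: 310.3 (620.6 in total);
- pooled variance throughout: 313.0 (626 in total).

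All three are within 3 % of 620. Other readings are not close: 20 % against 35 % without a margin gives 276, 20 % against 25 % gives 2188, and the margin test at one-sided 0.05 gives 480–494.

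**4. Power at 606.** With n per arm and 0.20 × 0.80 + 0.35 × 0.65 = 0.3875, power = Φ(0.10/√(0.3875/n) − 1.96).
- n = 310 (620 in total): Φ(0.868) = 80.7 %.
- n = 303 (606 in total): Φ(0.836) = 79.9 %.
- If 620 is instead taken to give exactly 80 %: Φ(2.802 × √(606/620) − 1.96) = 79.1 %.

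The loss is under 1 point either way.

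**5. The floor of 357.** The pre-loss figure is not printed. With a 1-point margin the effective difference is 0.14, and the unpooled formula gives 155.2 per arm, 310.4 in total; 310.4 × 1.15 = 356.9, so 357. Division gives 310/0.85 = 364.7, about 365. The back-calculation is not unique: the mixed-variance formula that best fits 620 gives 318 here, and 357 is also half of 713 rounded up (356.5). A factor of 1.15 lies behind either route to 357.
- 357 × 0.85 = 303.5.
- Power on the 1-point basis at 151.7 per arm: Φ(0.14/√(0.3875/151.7) − 1.96) = Φ(0.810) = 79.1 %.

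**6. Preconditioning injuries, illustration only.** The document gives no rate for these weeks.
- Constant hazard from the 20 % incidence: 1 − 0.80^(8/24) = 7.2 % if the 20 % is for 24 weeks; 1 − 0.80^(8/16) = 10.6 % if it is for 16 weeks.
- From exposure: Table 1 schedules 123 km. At an assumed 6 min/km that is 12.3 h, and the 7.7 per 1000 h cited in the Background gives 1 − exp(−0.0947) = 9.0 %. Over the cited study range of 2.5–33.0 per 1000 h it is 3–33 %.
- If 7.2 % to 10.6 % were injured, excluded, and not part of the 15 %: 713 × 0.85 × 0.928 = 562 and 713 × 0.85 × 0.894 = 542. By the formula in step 4, power is 76.8 % and 75.3 % (76.1 % and 74.5 % if 620 is anchored at 80 %).

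**The case against.** The strongest reply is that the proven error does almost nothing: 17 recruits, 2.4 % of the target, and less than one point of power. Runners censored after the intervention starts also still contribute time to the Kaplan-Meier and pseudo-value analysis, so counting each as wholly lost is conservative. Both points stand and limit the weight of the finding. They do not make 713 right, because the article itself counts loss that way and gives 713 as the number required.

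The margin basis is also inferred. Statistical analysis gives only a significance level ("Differences are considered statistically significant at" p < .05) and no margin for the test. Against a zero difference, a simple comparison of 20 % and 35 % with 303 per arm has power Φ(0.15/√(0.3875/303) − 1.96) = Φ(2.23), about 99 %. That is not the planned instrumental variable analysis, but it shows that the percentages above belong to one reading of the design.

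A reader might infer something stronger: that injuries before the intervention fall outside the 15 % and pull true power into the low or middle 70s. The document does not support that as a fact. The 15 % was set for the 24-week follow-up, which by definition includes the 8 preconditioning weeks, so it may already cover these runners. The article does not say how they are handled. Methods/design places randomization after preconditioning while Randomization places allocation at inclusion, so exclusion is an inference. Some injured runners could also recover in time, since an injury needs only 7 days of reduced training, although the cited median recovery of 72 days exceeds the 56 days available. What remains is an ambiguity to be resolved, not a demonstrated shortfall.

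**Conclusion.** The arithmetic error is certain for 713: on the article's own inputs the required number is 730. For 357 it is probable, because the 310 behind it is back-calculated. The consequence is minor: power of about 79–80 % at 606 and about 79 % at 303, given the margin reading, two-sided 0.05 and full loss of 15 %.

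Whether the 15 % covers injuries during preconditioning is undetermined. If it does, only the corrections to 730 and about 365 remain. If it does not, the shortfall would be larger, roughly 75–77 % power under the illustrative 7–11 %, but that range rests on assumed rates and assumed exclusion and should not be reported as the trial's power.

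**What to change.** In Power and in the Discussion, do one of the following:

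- replace 713 by 730 and 357 by about 365, and print the pre-loss figure for the floor; or
- keep 713 and 357 as recruitment numbers and state that after 15 % loss they leave 606 and 303 runners, with power just under 80 % on the basis used.

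In the same paragraphs, say that these numbers count inclusions, and whether the 15 % includes runners injured in the 8 preconditioning weeks. If it does not, add a separate allowance and give its assumed rate. For example, 620/(0.85 × 0.928) = 787 at 7.2 % and 620/(0.85 × 0.894) = 816 at 10.6 %.

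The cost is a rewording of two paragraphs. The first option asks for 17 more inclusions on the target and about 8 on the floor. The second asks for none but accepts slightly lower stated power. A separate preconditioning allowance would either raise the target further or lower the stated power.

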### Statistical analysis

All data will be analyzed using an instrumental variable approach in the primary analysis [36]. The instrumental variable is the randomization. Secondary analyzes are intention-to-treat and per-protocol. Time to first injury is analyzed using the following primary time scale: calender time in days and weeks. Data will be analyzed at the following time-points: 2 weeks, 4 weeks, 8 weeks and 16 weeks after randomization. Secondary time scales are cumulative running volume in kilometres and cumulative running volume in minutes. Time of follow-up begins when the randomized interventions start. The unit of analysis is each participant. Participants will be right-censored in case of pregnancy, disease, lack of motivation, non-running-related injury causing a permanent stop of running, unwillingness to attend clinical examination in case of injury, if more than 10 % of all training sessions were uploaded manually (they will be censored at the time 10 % of uploads are manual) or at end of follow-up, whichever comes first.

The injury proportion as a function of the follow-up time scales mentioned above will be estimated using the Kaplan-Meier curve. The cumulative injury risk difference between groups is analyzed, performing a generalized linear regression, using the pseudo values method [37]. Competing risk analysis will be performed separately for both groups, to investigate difference in risk of hypothesized injuries including more than one endpoint [38]. The Aalen Johansen estimator will be applied in the competing risks analysis. Endpoints included in the competing risk analysis are non-running-related injury causing a permanent stop of running and the 20 injuries presented by Taunton et al. [13] In the intensity group (Sch-I) the risk of achilles tendinopathy, gastrocnemius injuries, and plantar fasciitis are analyzed in a competing risk model, treating the remaining 17 injuries as competing events. In the volume group (Sch-V) the risk of patellofemoral pain syndrome, iliotibial band syndrome, and patellar tendinopathy are analyzed in a competing risk model, treating the remaining 17 injuries as competing events [21]. Differences are considered statistically significant at *p* < .05, and estimates are presented with 95 % confidence intervals. All analyzes are performed using STATA/SE version 13 (or more if applicable).

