#### Intervention training period

*Sch*-*I* (Intensity training group) is exposed to increased running volume at a hard pace (defined as an intensity equal to or above a VO2max of 88 %). The total running volume per week is fixed, and only kilometers at a hard running pace follow the progression in running. The running volume at a hard pace will increase in each 4 week progression cycle (Fig. 2). The remaining distance will be performed at an easy pace (defined as an intensity below a VO2max of 80 %).

*Sch*-*V* (Volume training group) is focused on increasing the total running volume per week. All scheduled running will be performed at either an easy or moderate pace (defined as an intensity equal to or below a VO2max of 88 %). Only the total running volume per week follows the progression in running (Fig. 2).

The intervention in both groups is presented in Fig. 2 and Tables 1, 2 and 3.

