### Outcome

The primary outcome is injury defined as a Running-Related Injury (RRI): *An injury sustained on muscles, joints, tendons and/or bones during or after running and attributed to running. The injury must have caused a training reduction (reduced distance, intensity, frequency etc.) for at least 7 days* [19], [34].

The secondary outcome is symptoms of overuse injury defined as: *A physical problem perceived as pain, tenderness, stiffness, aching, looseness, locking or instability in any part of the body* [25]. The information is collected using a modified version of the OSTRC questionnaire [25]. The modification of the questionnaire consists of an addition to the possible answers in the fourth and last question *“Cannot participate due to pain”*. The included anatomical areas are: foot, ankle, front of lower leg, calf, knee, thigh, hamstrings, groin, glutes, hip and lower back. An approach similar to the one used by Clarsen et al. [33], is applied to ease the response load on the participants.

All participants who report an RRI are referred to injury diagnosis, performed by a physiotherapist. Injury diagnosis is carried out using a standardized examination protocol and standardized diagnostic criteria [10]. The OSTRC questionnaire will continue to be administered to participants who are diagnosed with an injury, in order to explore the severity of injuries.

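### The risk difference is analysed at four unranked time points under one unadjusted p < .05, and no primary time point is named for H1

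*Protocol article*

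**What the plan says.** All references are to the protocol article.

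- **Statistical analysis, time points:** "Data will be analyzed at the following time-points: 2 weeks, 4 weeks, 8 weeks and 16 weeks after randomization".
- **Statistical analysis, between-group comparison:** "The cumulative injury risk difference between groups is analyzed, performing a generalized linear regression, using the pseudo values method".
- **Statistical analysis, threshold:** "Differences are considered statistically significant at" p < .05, with 95 % confidence intervals. No adjustment for several tests is mentioned and sidedness is not stated.
- **Statistical analysis, ranking:** the instrumental-variable analysis is primary, and intention-to-treat and per-protocol are secondary. Calendar time is the primary scale, and cumulative kilometres and minutes are secondary. The four time points have no such order.
- **Background, H1:** a 15 % increased injury risk with the intensity focus, with no horizon.
- **Outcome:** "The primary outcome is injury defined as a Running-Related Injury (RRI"), again with no horizon.
- **Power:** "an injury incidence of 20 % is expected in runners focusing on volume" and "an injury incidence of 35 % is expected in runners focusing on intensity"; for a minimum difference of 5 %, "a sample size of 620 participants is required to reach a power of 80" %. None of these figures is tied to a time point.
- **Intervention training period and Tables 2 and 3:** weekly volume in the intensity arm (Sch-I) is fixed and only its hard-pace kilometres progress. For the volume arm (Sch-V), "Only the total running volume per week follows the progression in running".

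**The concern.** H1 is a single hypothesis about overall injury risk, but the plan provides four estimates of the risk difference that could each be held against p < .05. Nothing says which one decides. After the data are seen, a significant result at 2, 4, 8 or 16 weeks could each be presented as the primary answer, and the stated 5 % error rate would no longer describe the procedure.

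The choice of horizon also affects interpretation. The two schedules separate in total volume only gradually, so an estimate at 2 weeks and one at 16 weeks compare the same randomized arms after quite different amounts of volume contrast.

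**Working it through.** **1. The plan's own sample size.** The figure of 620 is approximately reproduced as superiority by a 5-point margin, two-sided 5 %, 80 % power:

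- Unpooled variance: n per arm = [0.20 × 0.80 + 0.35 × 0.65] × (1.960 + 0.842)² / (0.15 − 0.05)² = 305, total 610.
- Pooled variance (mean risk 0.275): 313 per arm, total 626.

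Both are within 3 % of 620. The calculation contains one comparison at one level, with no allowance for four tests and no horizon.

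**2. Error rate if any of the four tests may count.**

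- If the tests were independent: 1 − 0.95⁴ = 0.185.
- The tests are nested, because an injury by week 2 also counts at weeks 4, 8 and 16. With cumulative risk F, the correlation of the risk differences at s < t is √{F(s)[1 − F(t)] / (F(t)[1 − F(s)])}.
- Assumption: constant hazard and the same risk in both arms, F(t) = 1 − (1 − F(16))^(t/16). With F(16) = 27.5 %, the midpoint of 20 % and 35 %, the risks at 2, 4, 8 and 16 weeks are 3.9, 7.7, 14.9 and 27.5 %.
- The correlations of week 2 with weeks 4, 8 and 16 are then 0.70, 0.48 and 0.33.

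| Assumed 16-week risk | P(any abs(Z) > 1.96) | abs(Z) needed for 5 % overall |
|---|---|---|
| 20 % | 14.4 % | 2.41 |
| 27.5 % | 14.5 % | 2.42 |
| 35 % | 14.6 % | 2.42 |

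(2 million normal draws each.) A binomial simulation with 310 per arm at 27.5 % gave 14.7 %.

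**3. What it would cost to keep all four as confirmatory tests.** With 310 per arm, the standard error at 20 % vs 35 % is √(0.3875/310) = 0.0354, so the margin test has expected Z = 0.10/0.0354 = 2.83.

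- One test at 5 %: power Φ(2.83 − 1.96), about 81 %.
- Bonferroni, 0.05/4 = 0.0125: Φ(2.83 − 2.50), about 63 %.
- Correlation-adjusted (nominal p about 0.016): Φ(2.83 − 2.42), about 66 %.

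**4. Scheduled exposure at the four points.** Tables 2 and 3, weekly volume column, summed from week 1 of the intervention period:

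| Up to week | Sch-I km | Sch-V km | Sch-V relative to Sch-I | Hard km, Sch-I / Sch-V |
|---|---|---|---|---|
| 2 | 37 | 37 | 0 % | 6 / 0 |
| 4 | 74 | 72 | −2.7 % | 11.7 / 0 |
| 8 | 148 | 150 | +1.4 % | 24.5 / 0 |
| 16 | 296 | 331.5 | +12.0 % | 52.9 / 0 |

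The Sch-I row for week 4 contradicts itself. Its volume column gives 18.5 km, but its paces sum to 13.8 + 2.7 = 16.5 km. By the paces, the totals are 72 vs 72 at week 4, 146 vs 150 (+2.7 %) at week 8 and 294 vs 331.5 (+12.8 %) at week 16. The pattern is the same on either reading.

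**The case against.** **The inflation is conditional.** The article nowhere says that significance at any one time point confirms H1. The p < .05 sentence is generic and covers the whole section. This stands: 14.5 % describes an any-of-four rule that the text permits but does not state. A reader might infer that the trial's error rate simply is three times 5 %, and the article does not support that.

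**The analysis plan may settle it.** A multiplicity rule is often left to that document, which is not shown. This carries some weight. But the article does fix the hierarchy of methods and of time scales in the same paragraph as the time points, and leaves only the time points level. That is an incomplete ranking in the published text, and more than omitted detail.

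**The calculation is simplified.** It uses plain risk differences, whereas the primary analysis is instrumental-variable with pseudo-values. This is so, and the figure should be read as approximate.

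**The early points are legitimate.** A reader might infer from the volume totals that the arms have the same volume at 2, 4 and 8 weeks and that those analyses do not address the trial's question. The tables do not support this. Cumulative volume is equal only at week 2 (and at week 4 if the Sch-I paces are summed). In weeks 5 to 7 the arms are already at 18.5 vs 20 km per week. From week 1, Sch-I has 3 km at hard pace where Sch-V has 3 km at moderate pace. The randomized contrast therefore exists at every time point, and the early estimates show the effect of the schedules up to that time.

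**Conclusion.** The point holds in a limited form. The article sets four unranked time points for the risk difference under one unadjusted threshold, and no other section supplies a primary horizon. If any of the four may confirm H1, the two-sided familywise error is about 14.5 % (14.4 to 14.6 % over 16-week risks of 20 to 35 %), with 18.5 % under independence. This assumes simple risk differences, a constant hazard, about 310 per arm, and two-sided testing inferred from the 95 % intervals.

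The volume figures are a supporting reason for choosing week 16, where the scheduled contrast reaches 12 %. They are not a reason to call the earlier analyses invalid.

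**What to change.** Add one sentence to the Statistical analysis section: the risk difference at 16 weeks from the start of the randomized schedules, on the calendar scale, is the single primary test of H1 at two-sided 5 %. State that the 2-, 4- and 8-week results and those on the kilometre and minute scales are secondary estimates with 95 % confidence intervals and no confirmatory claim. In the power section, tie the 20 % and 35 % to the same 16-week horizon. Separately, reconcile the week 4 row of Table 2.

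With a single test the error rate returns to 5 % and the sample size is unchanged. Week 16 also has the most events. The price is that an early difference, for example one that appears by week 4 and later fades, could be described but not claimed as confirmation. If the investigators want to keep that option, they should state an adjusted level for the four tests and accept a fall in power for the margin test from about 81 % to 63 to 66 % at 310 per arm.

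### One right-censoring list, including lack of motivation and manual uploads, is not limited to the per-protocol analysis, so as written it ends outcome follow-up in the instrumental-variable and intention-to-treat analyses

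*Protocol article*

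**What the plan says.** The protocol article's Statistical analysis section fixes the main analysis: "All data will be analyzed using an instrumental variable approach in the primary analysis". It adds that "The instrumental variable is the randomization" and that "Secondary analyzes are intention-to-treat and per-protocol".

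For time to first injury it then gives one list of censoring reasons: "Participants will be right-censored in case of pregnancy, disease, lack of motivation". The list continues with an injury from another cause that ends running for good, refusal of the clinical examination, more than 10 % of sessions uploaded manually ("they will be censored at the time 10 % of uploads are manual") and end of follow-up. No reason is tied to a particular analysis, and lack of motivation is not defined.

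Injury proportions come from Kaplan-Meier curves. For the effect estimate, "The cumulative injury risk difference between groups is analyzed, performing a generalized linear regression, using the pseudo values method".

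Outcome data do not depend on GPS uploads. The Data on outcome and Follow-up sections describe an OSTRC questionnaire sent every Sunday, with an automated reminder. The Outcome section keeps sending it to runners already diagnosed with an injury.

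**The concern.** An instrumental-variable analysis built on randomisation copes with non-adherence by using the outcomes of everyone as randomised. Intention-to-treat needs the same outcomes. Losing motivation arises after randomisation and may be a form of non-adherence. If it ends outcome follow-up, the later outcomes of those runners are missing from both analyses, and the results move towards the risk among runners who carry on.

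Kaplan-Meier and pseudo-values in their standard form also assume that censored runners would have had the same later risk as those who remain. That is doubtful here. Complaints that fall short of the 7-day injury definition can sap motivation, and a hard-pace schedule and a longer-distance schedule may do so to different degrees.

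The manual-upload rule has a similar fault. It censors people who are still running and reachable because of how their exposure data arrived, not because their outcome is unknown.

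**Working it through.** The plan gives no figure for the effect of censoring, so what follows is an illustration. The sample sizes of 620 and 713 play no part in it.

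**Inputs from the Power section:** injury risk 35 % (Sch-I) and 20 % (Sch-V), a difference of 15.0 points; expected loss to follow-up 15 %.

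**Assumptions:** constant hazards over the 16 weeks after randomisation; all loss is lost motivation; the split between arms; the injury hazard after stopping.

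**1. Stopping unrelated to injury risk.** With the 16 weeks as the time unit, λ = −ln(1 − injury risk) and δ = −ln(1 − stopping proportion).
- Censored analysis: Kaplan-Meier recovers 1 − exp(−λ), that is 35 % and 20 %, a difference of 15.0 points.
- Full follow-up with no injury after stopping: risk = λ/(λ+δ) × [1 − exp(−(λ+δ))], where exp(−(λ+δ)) = (1 − injury risk)(1 − stopping proportion).
- λ is 0.4308 (Sch-I) and 0.2231 (Sch-V). δ is 0.1625 for 15 %, 0.2231 for 20 % and 0.1054 for 10 %.

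Stopping 15 % in each arm:
- Sch-I: 0.4308/0.5933 × (1 − 0.65 × 0.85) = 0.7261 × 0.4475 = 32.5 %
- Sch-V: 0.2231/0.3857 × (1 − 0.80 × 0.85) = 0.5786 × 0.3200 = 18.5 %
- Difference 14.0 points

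Stopping 20 % (Sch-I), 10 % (Sch-V):
- Sch-I: 0.4308/0.6539 × (1 − 0.65 × 0.80) = 0.6588 × 0.4800 = 31.6 %
- Sch-V: 0.2231/0.3285 × (1 − 0.80 × 0.90) = 0.6793 × 0.2800 = 19.0 %
- Difference 12.6 points

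Stopping 10 % (Sch-I), 20 % (Sch-V):
- Sch-I: 0.4308/0.5361 × (1 − 0.65 × 0.90) = 0.8035 × 0.4150 = 33.3 %
- Sch-V: 0.2231/0.4463 × (1 − 0.80 × 0.80) = 0.5000 × 0.3600 = 18.0 %
- Difference 15.3 points

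Varying the hazard after stopping (numerical integration), as-randomised difference in points:

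| Stopping, Sch-I / Sch-V | No injury after stopping | Half the hazard | Same hazard |
|---|---|---|---|
| 15 % / 15 % | 14.0 | 14.6 | 15.0 |
| 20 % / 10 % | 12.6 | 13.9 | 15.0 |
| 10 % / 20 % | 15.3 | 15.2 | 15.0 |

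**2. Stopping related to injury risk.** Assume a quarter of each arm has 3 times the injury hazard of the rest, with hazards set so that the true risks stay at 35 % and 20 %. The other runners stop at 5 %. The Kaplan-Meier limit uses, at each time, the average hazard of those not yet injured or censored.

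| High-risk runners stopping, Sch-I / Sch-V | Kaplan-Meier Sch-I | Kaplan-Meier Sch-V | Difference (true 15.0) |
|---|---|---|---|
| 30 % / 30 % | 34.1 % | 19.4 % | 14.7 |
| 60 % / 30 % | 32.8 % | 19.4 % | 13.4 |
| 60 % / 10 % | 32.8 % | 19.9 % | 12.9 |

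With twice the hazard, the three differences are 14.8, 14.0 and 13.7. Even in the last row, overall stopping averages 12.5 %: Sch-I 0.75 × 5 % + 0.25 × 60 % = 18.75 %, and Sch-V 0.75 × 5 % + 0.25 × 10 % = 6.25 %. That is inside the planned 15 %.

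**The case against.** A reader might infer that the rule removes non-adherers and flatly contradicts the instrumental-variable and intention-to-treat analyses. The text does not support that.

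- Censored runners stay in their arm and count until the censoring time; only later follow-up is lost. Runners who skip sessions or miss pace or volume but carry on are not censored for that, so the instrumental-variable analysis still has non-adherence to handle.
- Lack of motivation may mean leaving the trial. It stands beside pregnancy, disease and a permanent stop of running, and the Power section brings in motivation when setting expected loss to follow-up. If no outcome can be obtained, censoring is ordinary practice in an intention-to-treat time-to-event analysis. What remains is then an untested independence assumption, not a contradiction.
- That the list governs every analysis is inferred from the absence of any restriction; the article does not say so. A fuller plan might set rules per analysis. Still, the list is a stated rule, not a detail left open.
- The figures in step 1 are partly a difference in target. The injury definition requires an injury attributed to running, so someone who no longer runs can hardly become a case. Those figures compare risk while running with risk counting stoppers as uninjured. Intention-to-treat asks the second question, so the gap is relevant, but it should not be described simply as bias.
- The roughly 60 % "completion of the scheduled running" in the Power section might be taken as a guide to how many would be censored. It describes sessions completed in other studies and is not a stopping rate.

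The manual-upload rule may serve the secondary time scales in kilometres and minutes, which depend on recorded running. That does not justify censoring on the calendar scale, where injury comes from the weekly questionnaire and clinical examination.

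**Conclusion.** The concern holds in a limited form. The rule as written does not separate stopping the schedule from leaving the trial, nor the per-protocol analysis from the other two. Under either meaning of lack of motivation it needs amending: reachable runners should be followed, and for unreachable ones the independence assumption should be tested.

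The size is modest and its sign is unknown. In the step 1 examples the as-randomised difference lies between 2.4 points below and 0.3 points above the 15.0 that the censored analysis targets, and the gap is zero if stopping leaves the hazard unchanged. In the step 2 examples the censored estimate falls 0.2 to 2.1 points short of 15.0. All of this rests on assumed stopping rates, arm splits and hazards after stopping, none of which the article gives. For scale, the Power section works with a minimum difference of 5 points. The matter should be corrected because it touches the primary analysis, but the documents do not show that the primary result would be invalid.

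**What to change.** For the instrumental-variable and intention-to-treat analyses on the calendar time scale:
- do not censor for lack of motivation or for manual uploads;
- keep sending the weekly OSTRC questionnaire to week 16 and count injuries in the randomised arm;
- censor only when outcome data are truly unobtainable.

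Define lack of motivation so that stopping the schedule and leaving the trial are recorded separately. Keep the adherence-related censoring for the per-protocol analysis. Add a sensitivity analysis for informative censoring, for example inverse-probability-of-censoring weights using the weekly OSTRC scores.

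The cost is a change of wording, one sensitivity analysis and continued use of an automated weekly e-mail that already exists. The downside is that some who stop will not answer and must still be censored.
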